### Analyses

2.14.

The study will be analyzed using quantitative and qualitative methods.

#### Quantitative analysis

2.14.1.

A repeated measures linear mixed-model will be used to estimate treatment effects for the combined sample, with HADS-A and HADS-D scores as outcomes, from pre-treatment, post-treatment and 6 months follow-up. Controlled effect sizes will be calculated in the following way: post treatment for immediate ATT minus post waiting list divided by the pooled standard deviation. Both ITT and per protocol analyses will be reported.

The primary reported analyses will be carried out as an intention-to-treat with all randomized participants. The analysis is supplemented with per-protocol analyses defined by participation in ≥4 of the 6 group-based sessions. Missing information on other co-variates will be permitted if there is <20% missing data for the co-variate in question. Age, gender, HADS-D and HADS-A scores will be entered in the models as covariates if baseline differences are observed.

An estimate of treatment effect size will be derived by comparing the wait-list control and intervention group on levels of symptoms of anxiety and depression (HADS), rumination (RRS), worry (PSWQ), insomnia (BIS), metacognitive beliefs (MCQ-30, PBRS, NBRS) and inflammation (CRP) at baseline, end of treatment and 6 months follow-up. False discovery rate will be applied for multiple testing (Benjamini and Hochberg, 1995).

Analyses will be undertaken using Stata SE vs. 18.0 (StataCorp, 2023) and/or R (R Core Team, 2021) and conducted by a statistician who will remain blind to group allocation throughout. A detailed statistical analyze plan (SAP) will be prepared and published prior to analyses taking place.

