**Methods:**

ATT-CHD is a randomized wait-list (WL) controlled study. Eligible CHD patients from two hospitals with Hospital Anxiety and Depression Scale (HADS)-Anxiety and/or HADS-Depression subscales scores ≥8 will be randomized into ATT (*n* = 32) or WL control (*n* = 32). After 6–8 weeks, WL patients will be allocated to ATT. Participants will be evaluated pre-, mid- and post-treatment, and at 6-months follow-up using changes in HADS as primary outcome. Secondary outcomes will be changes in psychiatric disorders, rumination, worry, type D-personality, metacognitions, insomnia, quality of life, and C-Reactive protein (CRP).

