### Data collection: participant timeline

2.9.

Patients will complete measures at baseline, mid-treatment, post-treatment and 6 months follow up. Details are shown in Table 1. No financial compensation will be provided to the participants.

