### Outcomes

2.11.

Primary outcomes are: changes in HADS-anxiety and HADS-depression scores from pre-treatment to post-treatment and 6 months follow-up between treatment arms. Changes in the proportion of patients scoring below 8 on HADS-anxiety and HADS-depression, respectively, from pre-treatment to post-treatment and 6-months follow-up between treatment arms.

Secondary outcomes are changes in psychiatric disorders, rumination, worry, type D-personality, insomnia, quality of life and metacognitions scores, as well as CRP levels, from pre-treatment to post-treatment and 6-months follow-up between treatment arms. In addition, qualitative data will be collected and evaluated.

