### Sample size and power calculation

2.13.

Statistical power calculation was based on the primary outcome of HADS with subscale outcomes of HADS-depression and HADS-anxiety. A conservative anxiety/depression effect size from previous studies of individual and group ATT for depression was used (0.67). This effect size is similar to what has been reported in a meta-analytic study of CBT and other psychological treatments (0.67) (Cuijpers et al., 2010). Thus, based on previous research, we expected a difference between the two conditions (ATT and WLC) amounting to an effect size of approximately 0.67. Allowing for 15–20% drop out in accordance with previous studies, we aim for a final sample size of 32 in each group, i.e., 64 in total. This yields a statistical power above 90% using a two-sided significance test (*p* < 0.05).

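### The primary HADS mixed model omits the planned mid-treatment score, so the post-treatment contrast can be biased if dropout follows early response differently in the two arms

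*Protocol article*

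**What the plan says.** Two places in the protocol article plan a mid-treatment assessment. The Methods paragraph of the abstract links it to HADS: "Participants will be evaluated pre-, mid- and post-treatment, and at 6-months follow-up using changes in HADS as primary outcome". Section 2.9 repeats the schedule without naming instruments: "Patients will complete measures at baseline, mid-treatment, post-treatment and 6 months follow up".

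Section 2.14.1 then lists the time points of the repeated-measures model for the primary outcome: "with HADS-A and HADS-D scores as outcomes, from pre-treatment, post-treatment and 6 months follow-up". The mid-treatment score is not among them, and the article states no other use for it, whether as a repeated measure, an auxiliary variable or an input to imputation.

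The list matches the endpoint in section 2.11: "changes in HADS-anxiety and HADS-depression scores from pre-treatment to post-treatment and 6 months follow-up between treatment arms". On the analysis population, section 2.14.1 says: "The primary reported analyses will be carried out as an intention-to-treat with all randomized participants". On attrition, section 2.13 says: "Allowing for 15–20% drop out in accordance with previous studies".

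**The concern.** A likelihood-based mixed model handles missing outcomes without bias only if, given the scores in the model, missingness does not depend on the missing values. A patient who stops between the middle and the end of treatment has a HADS score that shows how the first weeks went, but the stated model does not see it. If that patient also misses the 6-month visit, the model sees baseline only.

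The two arms ask different things of patients. One attends six weekly group sessions with daily homework (section 2.6); the other is monitored while waiting (section 2.7). It is plausible that reasons for leaving differ between them. If patients who are not improving leave ATT more readily than comparable patients leave the wait list, a model blind to early response overstates the benefit of ATT. With other patterns it understates it. What is at stake is the credibility of the missing-at-random assumption behind the main ATT versus wait-list contrast.

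**Working it through.** **Inputs from the article.** 32 per arm, effect size 0.67 SD and 15–20% dropout (section 2.13); model time points (section 2.14.1); mid-treatment assessment (abstract, section 2.9). The article gives no figure for dropout bias, so there is none to reproduce.

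**Assumed, because the article does not give them.** Correlations between pre, mid and post HADS, and the dropout rule:
- pre–mid 0.5–0.7, mid–post 0.6–0.8, pre–post 0.5–0.7;
- log-odds of dropout rising by 0.5–1.5 per SD of mid score;
- every dropout leaves after giving a mid score, and there is no 6-month score.

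The last line makes the result larger than it would be with earlier dropout or with retained 6-month data.

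**Step 1: what the mid score adds beyond baseline.** In SD units, the slope of post on mid, given pre, is (r_mid,post − r_pre,mid × r_pre,post) / (1 − r_pre,mid²). For correlations written as pre–mid / mid–post / pre–post:
- 0.6 / 0.7 / 0.5: (0.7 − 0.30)/0.64 = 0.63
- 0.7 / 0.8 / 0.6: (0.8 − 0.42)/0.51 = 0.75
- 0.5 / 0.6 / 0.5: (0.6 − 0.25)/0.75 = 0.47
- 0.7 / 0.7 / 0.7: (0.7 − 0.49)/0.51 = 0.41

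The slope is not zero in any of these sets, so dropout driven by the mid score is not fully repaired by conditioning on baseline.

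**Step 2: bias in one arm's post-treatment mean.** Normal scores were simulated for 400,000 patients per arm, with post missing by the logistic rule. The likelihood estimate of the post mean is the regression prediction of post averaged over everyone randomized, using pre only or pre and mid.

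| pre–mid / mid–post / pre–post | Log-odds per SD | Dropout | Bias, pre only (SD) | Bias, pre + mid (SD) |
|---|---|---|---|---|
| 0.7 / 0.7 / 0.7 | 0.5 | 15% | −0.016 | 0.000 |
| 0.6 / 0.7 / 0.5 | 1.0 | 15% | −0.051 | 0.003 |
| 0.6 / 0.7 / 0.5 | 1.0 | 20% | −0.073 | −0.001 |
| 0.7 / 0.8 / 0.6 | 1.5 | 20% | −0.098 | −0.004 |

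The first and last rows are the extremes of the grid: about 0.02 to 0.10 SD without mid, and about zero with it. Against the assumed effect this is 0.02/0.67 = 3% to 0.10/0.67 = 15%.

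**Step 3: bias in the arm difference.** Correlations 0.6 / 0.7 / 0.5, slope 1, true d = 0.67, mid score not in the model:
- same rule in both arms, 20% dropout: bias 0.002 SD, so d stays at 0.67;
- dropout driven by baseline only, 20%: bias 0.001 SD in the arm mean;
- high scorers leave ATT, wait-list dropout random, 15–20%: d = 0.72–0.74;
- as above, but the wait list has half the ATT slope: d = 0.70;
- high scorers leave ATT, but half of the dropouts leave at random before mid: d = 0.70–0.71; three quarters: about 0.69;
- informative dropout in the wait list only, or ATT responders leaving: d = 0.60–0.62;
- opposite rules in the two arms, 20%: bias about 0.15 SD.

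**Step 4: compare with sampling error.** 32 × 0.85 = 27.2 and 32 × 0.80 = 25.6, so about 27 or 26 per arm remain. The standard error of a difference in SD units is √(2/27) = 0.272 or √(2/26) = 0.277, before any gain from baseline adjustment. A one-arm bias of 0.10 SD is 0.10/0.272 = 0.37 of a standard error; 0.02 SD is 0.02/0.277 = 0.07.

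**The case against.** The strongest reply is that this belongs in the SAP, which section 2.14.1 promises before analysis, and that the model visits match the endpoint in section 2.11. Both facts are true, and no statement in the article is contradicted. But the article does not leave the model's time points open: it lists them, and an SAP that follows it will carry the omission forward. A visit can also inform the model without being an endpoint.

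Other parts of the reply stand and limit the point:
- **Predictive strength.** A reader might infer that the mid score is the best predictor of a missing post-treatment score. The article has no data on this; it is only a plausible predictor.
- **Presence and direction of bias.** A reader might infer that the stated model necessarily overstates the ATT effect. That needs dropout that occurs after mid-treatment, depends on the mid score beyond baseline and differs between arms in one particular direction. The article establishes none of these.
- **Baseline only.** A patient lost between mid and post may still return at 6 months, and that score is in the model.
- **Wait list.** The crosses in Table 1 are not legible in the text at hand, and section 2.7 mentions re-assessment only at the end of the wait. A mid-wait HADS is therefore not established.

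**Conclusion.** The point holds as a conditional weakness in a stated analysis choice. A planned HADS measurement is left out of the primary model, and including it would make missing at random easier to defend under 15–20% dropout.

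The size is small to moderate: about 0.02–0.10 SD in one arm's post-treatment mean under the assumed correlations and dropout slopes, with every dropout leaving after the mid score. The bias in the arm difference may be about zero, positive or negative. A statement that the effect will be inflated by a given percentage would describe one chosen scenario, and the article does not support it. Even the larger one-arm values are well below the standard error of 0.27–0.28 SD. The case for the change is that it costs almost nothing, not that the result is known to be wrong.

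**What to change.** In the SAP, enter mid-treatment HADS-A and HADS-D as an additional level of categorical time in the repeated-measures model, with unstructured covariance. If wait-list patients have no mid-wait HADS, enter that level for the ATT arm alone. Keep the ATT versus wait-list contrast at post-treatment/end of wait as the estimate of interest, so that the endpoint in section 2.11 does not change. State which arms have the mid score.

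The cost is a line in the SAP and a few more covariance parameters in a trial of 64; no new data collection is needed where the mid score is already planned. The limits are that patients lost before mid-treatment gain nothing, and that without a mid-wait score there is no correction in the wait-list arm.

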### Recruitment and allocation

2.5.

Consecutive patients hospitalized with a CHD event during the past years (2011–2022) at the department of cardiology at Drammen hospital or Vestfold hospital will be assessed for eligibility. All potentially eligible patients will be selected from hospital discharge lists by searching chronologically after last admission for the index event during the past years (2011–2022) prior to study inclusion. A specially-trained research cardiac nurse will screen the hospital records. All eligible patients (*N*⁓1,500) will be mailed a comprehensive self-report questionnaire as part of a follow up study addressing psychological distress. The responses will be screened by a research nurse and those who score ≥ 8 for HADS-A and/or HADS-D will be mailed information about the ATT-CHD study and consent to be contacted for further information and evaluation if they return a signed informed consent form together with a recent score ≥ 8 on either of the HADS subscales. Those who meet our eligibility criteria will be offered a face-to-face evaluation, and information about the study if eligible. Those who consent to participate will undergo diagnostic interviews as well as self-report assessments before being randomized and allocated to either ATT immediately or wait-list control. Randomization will be performed by a study statistician blinded to the results of the evaluations. An online software tool is used for randomization with a block- and list-size of 8–12 persons (Sealed Envelope Ltd, 2022. Create a blocked randomization list^1^). The randomization program will be kept in a secured, logged hard disk. Before randomization, baseline data will be collected (Table 1).

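### Baseline HADS, age and gender are adjusted for only if the arms are seen to differ: a data-dependent rule without a criterion, paired with an unadjusted effect size

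*Protocol article*

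**What the plan says.** Three statements in the protocol article, section 2.14.1 (Quantitative analysis), bear on how baseline is used.

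- Covariates: "Age, gender, HADS-D and HADS-A scores will be entered in the models as covariates if baseline differences are observed". The section does not say what counts as a difference, or which HADS score goes into which model.
- Primary model: a repeated measures linear mixed model "with HADS-A and HADS-D scores as outcomes, from pre-treatment, post-treatment and 6 months follow-up". Pre-treatment HADS is therefore one of the response occasions. Whether the arms share a common baseline mean is not stated.
- Controlled effect size: "post treatment for immediate ATT minus post waiting list divided by the pooled standard deviation". Baseline does not enter this formula.

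Section 2.13 plans on a difference "amounting to an effect size of approximately 0.67" and says "we aim for a final sample size of 32 in each group, i.e., 64 in total". Section 2.5 describes the allocation: "An online software tool is used for randomization with a block- and list-size of 8–12 persons". It names no stratification factor.

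**The concern.** The reason to adjust for baseline HADS is that it can be expected to predict later HADS. That holds whether or not the arms happen to differ. A rule triggered by observed imbalance ties the model to a chance event and leaves its form undecided until the data are in. Taken literally, two sample means of a score always differ somewhat, so the rule could mean always adjust, sometimes adjust, or adjust when someone judges the gap large.

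Chance imbalance is realistic here. There are 32 patients per arm and no stratification. Entry requires a raised score on only one of the two HADS subscales (section 2.4), so patients may be low on the other.

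Three things are at stake: precision, if the fallback analysis makes poor use of baseline; the reported effect size, which takes up imbalance directly; and a clear specification, because the trigger could place pre-treatment HADS on both sides of the same model.

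**Working it through.** **Inputs.** From section 2.13: standardised difference d = 0.67, 32 per arm, two-sided 5% test, dropout 15–20%. Not in the document, and therefore assumed: the baseline-to-post correlation r (range 0.3 to 0.7), equal SDs at both occasions, and a trigger of p<0.05 in a baseline t-test.

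**1. The plan's own power figure.** The protocol says: "This yields a statistical power above 90% using a two-sided significance test". With SE = √(2/32) = 0.25, d/SE = 0.67/0.25 = 2.68, and power = Φ(2.68 − 1.96) = Φ(0.72) = 76.4% (75.1% with the t distribution). The stated figure is not reproduced. That is a separate point. Here it only sets the unadjusted reference value.

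**2. Size of chance imbalance.** The baseline mean difference has SD √(2/32) = 0.25 SD units, so 95% of trials fall within ±0.49. An imbalance of 0.4 gives z = 0.4/0.25 = 1.6, p about 0.11, and would not trip a p<0.05 trigger.

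**3. Effect on the controlled effect size.** Given a baseline imbalance b, the raw post-score difference shifts on average by r × b. With r = 0.5 and b = 0.4 this is 0.20, and 0.20/0.67 = 30% of the planned effect.

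**4. Analytic power for fixed analyses, 32 per arm.** Residual SD is 1 for post-only, √(2(1−r)) for an unconstrained change contrast and √(1−r²) for baseline adjustment. Example at r = 0.5: 2.68/√0.75 = 3.095, and Φ(3.095 − 1.96) = 87.2%.

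| r | post-only | change | adjusted |
|---|---|---|---|
| 0.3 | 76.4% | 62.0% | 80.2% |
| 0.5 | 76.4% | 76.4% | 87.2% |
| 0.6 | 76.4% | 85.0% | 91.8% |
| 0.7 | 76.4% | 93.3% | 96.3% |

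A mixed model that has baseline as a response and constrains the baseline means to be equal performs about as the adjusted column does.

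**5. The conditional rule itself.** Simulation with 40,000 trials per setting, 32 per arm, complete data, adjusting only if baseline p<0.05:

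| r | fallback | conditional | always adjust | loss (points) |
|---|---|---|---|---|
| 0.3 | post-only | 75.5% | 78.5% | 3 |
| 0.5 | post-only | 75.9% | 85.6% | 10 |
| 0.7 | post-only | 77.3% | 95.5% | 18 |
| 0.3 | change | 61.5% | 78.3% | 17 |
| 0.5 | change | 76.2% | 85.8% | 10 |
| 0.7 | change | 92.8% | 95.5% | 3 |

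Against a baseline-constrained mixed model the loss is about nil.

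**6. Type I error.** Under no effect the conditional rule rejects in 3.6% to 4.8% of trials at the 0.05 trigger, and in as few as 2.5% at a 0.20 trigger. It is conservative, not inflated.

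**The case against.** The strongest reply is that the planned mixed model already contains pre-treatment HADS as a response, so baseline is not ignored. If the arms share a baseline mean, the covariate rule costs almost nothing. This stands. It means that no single power loss can be attributed to the protocol, and a loss near zero is compatible with its text.

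Safeguards are also stated: the statistician stays blind to allocation, and a detailed SAP is to be published before analysis. These limit outcome-driven choice of model. They do not cure the rule, because it is a stated instruction rather than a gap left for the SAP, and a SAP that follows it inherits the fault.

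The controlled effect size is a summary and is not named as the primary test. A loss of precision calculated for a raw post-score comparison therefore does not carry over to the primary analysis. The shift in the reported effect size remains.

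A reader might go on to infer four stronger things, none of which the document supports:

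- That the rule costs a definite 10 points of power. This needs r near 0.5, a p<0.05 trigger and a fallback that uses baseline poorly. The protocol states none of them.
- That false positives are inflated. The simulated rates lie below 5%.
- That using baseline as both response and covariate biases the treatment effect. In four simulated complete data sets with a random-intercept model, adding baseline left the group-by-time estimate unchanged and lowered its SE by about 2–5%. This is poor specification, without demonstrated bias.
- That adjusting for age and gender would raise power. The document gives nothing from which such a gain could be computed.

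**Conclusion.** The point holds in a limited form. The covariate rule depends on the data, has no criterion and rests on a poor reason for choosing covariates. The controlled effect size takes up chance imbalance: about 0.2, or 30% of the planned 0.67, for a 0.4 SD imbalance at an assumed r of 0.5. The possible double use of pre-treatment HADS needs to be ruled out.

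The power cost is conditional. It is about 3 to 18 points for assumed r of 0.3 to 0.7 with a post-only or change-contrast fallback and an assumed p<0.05 trigger, and about nil if baseline means are constrained to be equal, which section 2.14.1 does not state. These figures assume normal data, equal SDs and 32 complete cases per arm. The defect in the rule is certain. The size of the loss is not.

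**What to change.** Replace the covariate sentence with a rule that the primary analysis always adjusts for the baseline value of the outcome (HADS-A in the HADS-A model, HADS-D in the HADS-D model), whatever differences are observed. Fix one form only:

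- ANCOVA-type adjustment, with post-baseline scores alone as responses; or
- a constrained longitudinal model, with baseline as a response and a common baseline mean across arms.

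Do not enter baseline as both response and covariate. Decide in advance whether age and gender are included, and not by observed imbalance. Compute the controlled effect size as the baseline-adjusted mean difference divided by a pooled SD, and say which occasion that SD comes from.

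The cost is a few sentences in the SAP and one or a few model degrees of freedom. All the variables are already in the planned baseline collection (sections 2.5 and 2.12.3), so no extra patients, visits or measurements are needed.

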##### Bergen Insomnia Scale (BIS)

2.12.2.5.

The BIS (Pallesen et al., 2008) is a six-item questionnaire based on the criteria for the clinical diagnosis of insomnia described in the *Diagnostic and Statistical Manual of Mental Disorders*, fourth version (DSM-IV-TR). The first four items inquire about difficulties with sleep initiation, maintenance of sleep, awakenings in the morning, and nonrestorative sleep; items five and six assess daytime impairment and satisfaction with sleep. A 30 min cutoff value is used for the first three items. All items are scored as number of days per week (0–7), yielding a continuous sum score from 0 to 42 (BIS sum score), increasing with severity of insomnia symptoms. The BIS can also be used as a diagnostic tool (insomnia vs. no insomnia). Three days or more on items one, two, three, or four combined with 3 days or more on item five or six indicate a diagnosis of insomnia. The BIS has adequate psychometric properties, and there are normative Norwegian data for comparison (Pallesen et al., 2008). In the present study, the 4-week test–retest reliability of the BIS was 0.92 (Peersen et al., 2017). The BIS was included in this study because BIS-insomnia has been associated with poor prognosis in CHD patients (Frøjd et al., 2022a) and our previous feasibility study demonstrated ATT to reduce insomnia (Dammen et al., 2022).

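### Secondary outcomes are defined as changes from pre-treatment but estimated from levels, with no stated rule that uses each outcome's own baseline

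*Protocol article*

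**What the plan says.** **Outcome definition (2.11, Outcomes).** "Secondary outcomes are changes in psychiatric disorders, rumination, worry, type D-personality, insomnia, quality of life and metacognitions scores, as well as CRP levels", measured "from pre-treatment to post-treatment and 6-months follow-up between treatment arms. In addition, qualitative data will be collected and evaluated". The quantity is a change, compared between arms.

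**Estimate (2.14.1, Quantitative analysis).** The effect estimate is to be "derived by comparing the wait-list control and intervention group on levels of symptoms of anxiety and depression (HADS), rumination (RRS), worry (PSWQ", followed by insomnia, metacognitive beliefs and "inflammation (CRP) at baseline, end of treatment and 6 months follow-up". The quantity is a level, and baseline is one of the time points at which the arms are compared.

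**Effect-size formula (2.14.1).** "post treatment for immediate ATT minus post waiting list divided by the pooled standard deviation". It has no baseline term.

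**Model (2.14.1).** "A repeated measures linear mixed-model will be used to estimate treatment effects for the combined sample, with HADS-A and HADS-D scores as outcomes". No model is named for the secondary scales or CRP.

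**Covariates (2.14.1).** "Age, gender, HADS-D and HADS-A scores will be entered in the models as covariates if baseline differences are observed". RRS, PSWQ, BIS, MCQ-30, PBRS, NBRS and CRP are not on that list.

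Section 2.5 states that baseline data are collected before randomisation. Section 2.14.1 promises a detailed SAP, published before the analyses.

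**The concern.** Two sections of the article describe the same treatment effect in different ways. One subtracts the pre-treatment value and the other does not. The second also lists a between-arm comparison at baseline as a source of the effect estimate, although a difference that exists before treatment starts carries no treatment effect.

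A trial of 64 patients can easily show a chance baseline difference on a symptom or trait scale. A level comparison carries that difference in full into the result. A change score subtracts all of it, and baseline adjustment removes the part that predicts the later value. Both of the first two are in print, so either could be presented as the planned analysis. Neither is the most precise use of baseline values that the trial already collects.

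**Working it through.** The article gives no power or precision figure for the secondary outcomes; section 2.13 concerns HADS only. There is therefore no plan figure to reproduce here.

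**Inputs**
- 32 patients per arm and 15–20% dropout (2.13).
- BIS: "reliability of the BIS was 0.92", a 4-week test-retest value (2.12.2.5). This is the only repeat-measure correlation in the article.
- Pre-post correlations r = 0.3, 0.5 and 0.7 for the outcomes: assumptions.
- Equal SDs across arms and time points, scaled to 1: assumption.

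**1. How far the two estimates can differ.** Let D1 be the between-arm difference after treatment and D0 the difference at baseline. The level estimate is D1 and the change estimate is D1 − D0, so they differ by exactly D0. Under randomisation D0 has mean 0, so both target the same mean effect. At 32 per arm its SD is √(2/32) = 0.25, and its 95% range is ±1.96 × 0.25 = ±0.49 SD units.

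**2. Precision.** Variance of the between-arm estimate relative to unadjusted levels:
- level: 1
- change score: 2(1 − r)
- adjusted for own baseline: 1 − r² (large-sample)

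The 95% half-width at 32 per arm is 1.96 × √(2v/32), where v is the relative variance. For unadjusted levels it is 0.49 SD at every r.

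| r | variance, change | variance, adjusted | half-width, change | half-width, adjusted |
|---|---|---|---|---|
| 0.3 | 1.40 | 0.91 | 0.58 | 0.47 |
| 0.5 | 1.00 | 0.75 | 0.49 | 0.42 |
| 0.7 | 0.60 | 0.51 | 0.38 | 0.35 |

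Change scores are worse than levels below r = 0.5, equal at 0.5 and better above it. Adjustment is never worse than either: 1 − r² ≤ 1, and 1 − r² = (1 − r)(1 + r) ≤ 2(1 − r).

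At r = 0.92 the factors would be 2 × 0.08 = 0.16 (change) and 1 − 0.8464 = 0.15 (adjusted). This is at most an upper bound, because test-retest reliability is not the pre-post correlation in a selected sample in which one arm is treated.

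**3. The same in power terms.** Take an assumed effect of 0.5 SD, 26 per arm (32 × 0.8 ≈ 26), two-sided 5%, and a two-sample t-test with the effect divided by √v. Levels give 42%. Change scores give 32%, 42% and 63% at r = 0.3, 0.5 and 0.7. Baseline adjustment gives 46%, 53% and 70%.

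**The case against.** **The SAP will settle it.** A condensed article may leave the model for each secondary outcome to the SAP, and silence alone would be no finding. That stands as far as it goes. But the article is not silent: it states a change in one section and a level comparison in another, and a SAP must depart from one of them.

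**A repeated-measures reading is possible.** The level sentence also names HADS, which has a mixed model, and its time points match that model's. If the arms are compared over all three occasions, the arm-by-time contrast is the difference in change that 2.11 describes. The post-score formula may be only a standardised summary. This reading is not excluded, so it cannot be said that the plan certainly ignores baseline. It is also not stated for any secondary outcome.

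**The covariate list may not be closed.** Section 2.14.1 has a missing-data rule for other covariates, so a reader should not infer that only the four named variables can ever enter. What holds is narrower: no stated rule brings in a secondary outcome's own baseline.

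**The precision loss depends on r.** A reader might infer that the level analysis wastes most of the available precision. The article does not support that in general. It gives no correlation for six of the seven outcomes, calling PSWQ a trait measure is not a correlation, and at r = 0.3 adjustment saves only 9% of the variance. Against the change definition in 2.11, levels are the more precise choice below r = 0.5.

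**Conclusion.** The mismatch between 2.11 and 2.14.1 is real, and it should be resolved before analysis. It concerns the secondary outcomes only. The missing-baseline point does not extend to HADS, which has a named model and conditional covariates.

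It would be wrong to conclude that the two definitions target different effects or that the level analysis is biased. In expectation they agree; in one realised trial with 32 per arm they differ by a chance amount with a 95% range of about ±0.49 SD. That size needs only equal SDs and randomisation, and does not depend on r.

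The precision gain from always adjusting for own baseline is conditional: 9%, 25% and 49% of the level variance at r = 0.3, 0.5 and 0.7, and none at r = 0. These correlations are assumed.

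**What to change.** State one estimator in 2.11, 2.14.1 and the pending SAP for every continuous secondary outcome: RRS, PSWQ, BIS, MCQ-30, PBRS, NBRS and CRP, and also the SF-12 and DS14 scores, which 2.11 covers as quality of life and type D personality but the level sentence omits. Suggested wording:

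*The treatment effect is the between-arm difference at end of treatment (immediate ATT) or end of waiting list (control), adjusted in all cases for that outcome's own pre-randomisation value. An equivalent mixed model with baseline means constrained equal across arms may be used.*

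Then:
- Remove the between-arm contrast at baseline as a treatment-effect estimate.
- Do not make own-baseline adjustment depend on whether a baseline difference is seen.
- Keep the 6-month comparison as a separate baseline-adjusted analysis labelled immediate versus delayed ATT, since by then the waiting-list arm will also have been offered ATT.

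The cost is wording. The baseline values are already collected, so no patients or measurements are added. Randomisation began in November 2022, and 10 of 64 patients had been included and followed up by May 2023 (2.17). The change to 2.11 should therefore be dated and recorded as a clarification made before analysis.
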